**Figure 2. F2:**
[figure not shown]
Stepped-wedge design matrix across six clinical clusters over 6 months. The figure illustrates the staggered transition from usual care (gray) to the digital intervention phase (blue) following a 2-week transition period (light blue).

### Patient Recruitment

Due to the dynamic turnover of psychiatric hospitalizations, an open-cohort approach was adopted, allowing for continuous recruitment throughout the study period. Recruitment follows a structured clinician-referral model across the 6 clinical units to ensure both clinical appropriateness and implementation fidelity. The process is organized into the following stages: Treating psychiatrists identify potential participants during routine clinical encounters in the outpatient and inpatient departments. Patients are considered for referral if they meet three prerequisites: (1) a BMI ≥24 kg/m², (2) a demonstrated interest in weight management, and (3) a confirmed stable clinical phase, defined as a minimum of 4 weeks on a stable medication regimen.

Upon referral, an independent project physician conducts a formal in-person screening session. This involves a review of the patient’s electronic health records (EHR) to confirm *ICD-10* (*International Statistical Classification of Diseases, Tenth Revision*) diagnoses and physical measurements of height, weight, and blood pressure. To ensure the validity of historical data, the exclusion criterion regarding significant prior weight loss is ascertained through a multi-informant approach, cross-referencing patient interviews with collateral reporting from family caregivers and EHR data. Detailed inclusion and exclusion criteria are summarized in Textbox 1.

Textbox 1.Inclusion and exclusion criteria.
**Inclusion criteria**
Age 18-60 years.*ICD-10 (International Statistical Classification of Diseases, Tenth Revision*) diagnosed schizophrenia or bipolar disorder.Overweight (BMI ≥24 kg/m² is defined as overweight or obese according to Chinese national standards).Current use of ≥1 antipsychotic or mood stabilizer (eg, lithium and valproate).Owning a smartphone and capable of reading.Expecting to remain in the study throughout the entire study period.
**Exclusion criteria**
Inability to provide informed consent in line with ethical requirements.≥7% weight loss in the past 6 months.“Secondary obesity” (such as hyperthyroid).The weight >150 kg.Pregnancy or planning pregnancy.Cardiovascular contraindications.Current participation in other trials.

### Informed Consent and Capacity Assessment

Due to the dynamic turnover of psychiatric hospitalizations (average stay 4‐6 wk), we use a consecutive, open-cohort recruitment model. Treating psychiatrists identify potential participants during routine clinical encounters. To prevent anticipation bias, crossover dates are disclosed to each unit’s implementation team only 2 weeks prior to their scheduled transition. This separation of roles ensures that the recruitment process remains objective and independent of the unit’s study phase. Given the vulnerability of the SMI population, a structured capacity assessment is conducted prior to enrollment. Participants must demonstrate comprehension of the study’s procedures, data workflows, and the right to withdraw. Written informed consent is obtained from all participants, with primary family caregivers strongly encouraged to witness the process and co-sign the form to provide an additional layer of advocacy. Signed documents are encrypted and stored securely at the research center.

To systematically assess the representativeness of the study sample, a comprehensive screening log is maintained for all identified patients. We record de-identified demographic and clinical data (age, sex, primary diagnosis, and EHR-derived BMI) for all screened candidates, including those excluded due to lack of smartphone access, weight limits (>150 kg), or refusal to participate. At the trial’s conclusion, a comparative analysis between enrolled participants and the broader hospital population will be performed to quantify recruitment bias and characterize the digital divide within the SMI population.

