## Methods

### Study Design

This study uses a pragmatic, open-cohort SW-CRT with a 2-month step duration. The trial spans a total observation window of 6 months across 6 clinical units at a tertiary hospital in Beijing. The SW-CRT design ensures that all participants eventually receive the intervention, fulfilling ethical requirements for this high-risk population, while the staggered rollout allows the implementation team to maintain high fidelity by providing intensive technical training for 1 wave at a time.

The trial addresses the dynamic turnover of psychiatric hospitalizations (average stay 4‐6 wk) by defining each cluster as a clinical unit rather than a fixed physical location. The research team comprises trained research assistants, certified nutritionists, and sports physicians. Participants are typically enrolled during their stable recovery phase in the ward; however, the intervention is designed to be portable. Following discharge, the intervention continues remotely, with the same clinical team providing longitudinal oversight via digital clinician dashboards. This approach enables the evaluation of the intervention across the transition from inpatient care to community-based recovery.

The 6 units were randomized into 2 waves (3 units per wave) using a matched-pair constrained randomization approach. To ensure baseline balance, units were paired based on clinical setting and demographics. Allocation was managed by an independent biostatistician via REDCap (Research Electronic Data Capture; Vanderbilt University) and remained concealed from the recruitment staff and participants.

The study timeline is structured into three distinct phases:

Baseline phase (month 1): all clusters receive usual care to establish stable baseline metrics.Transition phase (2 weeks): a staggered 2-week period for device distribution and technical training, occurring at month 1 for wave 1 and month 3 for wave 2.Intervention phase: active digital monitoring lasting 5 months for wave 1 (months 2-6) and 3 months for wave 2 (months 4-6).

This open-cohort approach accounts for the dynamic turnover of psychiatric hospitalizations, allowing for individual enrollment while maintaining randomization at the cluster level (Figure 2).

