#### Secondary Outcomes

To address the limitations of binary variables and capture broader metabolic health improvements, we have established a clear hierarchy of secondary endpoints:

Key clinical markers: these include the absolute change in body weight (kg) and BMI, body fat percentage, and metabolic markers (fasting blood glucose and lipid profiles). Weight metrics are automatically recorded via the Huawei Pro 3 smart scale.Implementation feasibility: feasibility is measured by device pairing success rate and intervention adherence. While participants are instructed to perform weekly weigh-ins and daily dietary logging, “Good adherence” for analysis purposes is operationally defined as completing ≥50% of expected weekly weigh-ins (ie, at least 2 weigh-ins per month) and logging dietary intake on ≥50% of days during the intervention period. Acceptability is assessed via the System Usability Scale (SUS) and semistructured interviews with 30 purposely selected participants (Multimedia Appendix 3).Psychosocial and functional outcomes: we use validated Chinese versions of psychometric scales with established reliability (Cronbach α>0.80) [33-42]:

Clinical symptoms: Patient Health Questionnaire-9 (PHQ-9) for depression, Generalized Anxiety Disorder-7 (GAD-7) for anxiety, Brief Psychiatric Rating Scale Version 4.0 (BPRS-4) for acute psychopathology, and Mood Disorder Questionnaire (MDQ) for mood swings.Functioning and quality of life: Sheehan Disability Scale (SDS) for functional impairment and Quality of Life Enjoyment and Satisfaction Questionnaire-Short Form (Q-LES-Q-SF) for life satisfaction.Cognitive and physical well-being: Perceived Deficits Questionnaire–Depression, 5-item (PDQ-D5) for subjective cognitive deficits, Chalder Fatigue Scale (CSF-11), Perceived Stress Scale (PSS), and Arizona Sexual Experience Scale (ASEX).Weight motivation: a 0‐100 mm Visual Analogue Scale (VAS) quantifies the intent to lose weight.

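### With two waves and two fixed dates, wave 2's allocation can be inferred once wave 1 is known, so the concealment claims do not hold as written for most of wave 2's control time

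*Protocol article*

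**What the plan says.** All references are to the Protocol article.

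- **Randomization (Study Design):** "The 6 units were randomized into 2 waves (3 units per wave) using a matched-pair constrained randomization approach". Beforehand, "units were paired based on clinical setting and demographics". All six units belong to one hospital.
- **Dates (Study Design):** each wave has a 2-week transition for handing out devices and training, "occurring at month 1 for wave 1 and month 3 for wave 2". The active phase is months 2-6 for wave 1 and months 4-6 for wave 2, and the step is 2 months.
- **Concealment (Study Design):** allocation "remained concealed from the recruitment staff and participants".
- **Guard against anticipation (Informed Consent and Capacity Assessment):** "To prevent anticipation bias, crossover dates are disclosed to each unit’s implementation team only 2 weeks prior to their scheduled transition". The section then concludes: "This separation of roles ensures that the recruitment process remains objective and independent of the unit’s study phase".
- **Referral (Patient Recruitment):** recruitment is continuous. Treating psychiatrists pick out candidates, and one condition for referral is "a demonstrated interest in weight management". An independent project physician screens those who are referred.
- **Motivation measure (Secondary Outcomes):** "a 0‐100 mm Visual Analogue Scale (VAS) quantifies the intent to lose weight".

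**The concern.** Telling each unit its date only 2 weeks ahead works when a unit that has heard nothing remains uncertain. With two waves and two dates, silence is informative. A unit that gets no notice when wave 1's notice falls due is in wave 2, and only month 3 is left for its crossover. Pairing makes this quicker, because knowing one unit's wave gives its partner's.

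Referral is where this could matter. Treating psychiatrists decide whom to refer, partly on the patient's interest in weight management, and the trial is open-label. If they know when devices will arrive, referral can depend on study phase or wave. The project physician acts only after referral and cannot see patients who were never put forward. Wave 2 supplies 9 of the 12 control unit-months on the article's calendar, and all control data after wave 1 crosses over. The confounders named under Covariate Adjustment and Confounder Control (exposure duration, antipsychotic risk group, medication possession) do not measure motivation to lose weight.

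**Working it through.** **1. The article's timeline reproduces.** Months 2-6 are 6 − 2 + 1 = 5 months. Months 4-6 are 6 − 4 + 1 = 3 months. Month 3 minus month 1 is the 2-month step. With 1 month = 365.25/12/7 = 4.35 weeks, a full month 1 plus 2 weeks plus 5 months is 28.1 weeks, against 26.1 weeks in 6 months. The transition therefore fits best inside months 1 and 3. Because the text is not explicit, three readings are tried below.

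**2. Allocations left once wave 1 is known.** Six paired units make three pairs (inferred). With one unit of each pair per wave there are 2³ = 8 allocations; without pairing there are C(6,3) = 20. Knowing the wave 1 set leaves exactly 1 in either case. Knowing that one unit is in wave 1 puts its partner in wave 2.

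**3. Share of wave 2's control time with foreknowledge.** Let t1 and t2 be the starts of the two transitions. Wave 1's notice comes at d1 = max(0, t1 − 2 weeks), and wave 2's control time ends at t2. The share is (t2 − d1)/t2. If wave 2 learns only when wave 1 receives devices, it is (t2 − t1)/t2. If it learns only when wave 1's active phase starts, it is (t2 − t1 − 2)/t2.

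| Reading of the transition | d1 (wk) | t2 (wk) | From wave 1's notice | From devices | From active phase | Intended by the rule (2/t2) |
|---|---|---|---|---|---|---|
| Last 2 weeks of months 1 and 3 | 0.35 | 11.04 | 10.7 wk, 97% | 79% | 61% | 18% |
| Starts at end of months 1 and 3 | 2.35 | 13.04 | 10.7 wk, 82% | 67% | 51% | 15% |
| Starts at beginning of months 1 and 3 | 0 | 8.70 | 8.7 wk, 100% | 100% | 77% | 23% |

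Foreknowledge is about 9-11 weeks if it dates from wave 1's notice, and at least 51% of wave 2's control time in every cell.

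**4. Illustration of what selection could do (assumptions, not data).** Take a calendar clock, even recruitment and no treatment effect. Suppose half of candidates are keen, with usual-care success of 30% against 10% in the rest, which averages to the plan's 20%. A fraction h of keen wave 2 patients is held back for 2 months and enrolled over the next 3.

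- Affected wave 2 control window: (0.5(1−h)×0.30 + 0.5×0.10)/(1 − 0.5h) = 18.6% for h = 0.25 and 16.7% for h = 0.50.
- Wave 2 recruits after crossover: the keen share is (0.5 + 0.5h×2/3)/(1 + 0.5h×2/3) = 53.8% or 57.1%, so untreated success is 20.8% or 21.4%.
- The gap within wave 2 is 2.2 or 4.8 points.

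The whole trial has 3×1 + 3×3 = 12 control and 3×5 + 3×3 = 24 intervention unit-months. Only 6 of the 12 control unit-months are in the hold-back window. Weighting by recruits:

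- Control, h = 0.25: (6×0.20 + 6×0.1625)/(6 + 6×0.875) = 2.175/11.25 = 19.3%. For h = 0.50: (1.2 + 6×0.125)/(6 + 6×0.75) = 1.95/10.5 = 18.6%.
- Intervention, h = 0.25: (15×0.20 + 9×0.225)/(15 + 9×1.083) = 5.025/24.75 = 20.3%. For h = 0.50: (3 + 9×0.25)/(15 + 9×1.167) = 5.25/25.5 = 20.6%.
- The crude gap is about 1.0 or 2.0 points, against the planned 20-point difference. A time-adjusted estimate could differ and was not computed.

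**The case against.** **Units may not have known the schedule.** No section says that units were told the number of waves, the dates or their partner. The article itself cannot have told them, since it reports follow-up as finished. Formal notice goes to implementation teams, not to referring psychiatrists. This stands as a limit: spread of the knowledge is an inference. It does not restore the claim. Device distribution and training in the same hospital are hard to hide, and even learning only from wave 1's active phase leaves more than half of wave 2's control time exposed. The separation of roles is asserted without showing that referring and implementing clinicians are different people. Study Design has the same clinical team overseeing patients after discharge.

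**Holding patients back may not make sense.** Visits at months 0, 1, 2, 3 and 6 (Outcomes and Measures), with data collection from May 2023 to June 2025 (Results), point at least as much to a 6-month clock for each participant. On that clock a wave 2 patient would start in usual care whenever referred, so waiting gains nothing. Even on a calendar clock, everyone eventually receives the intervention, average stays are 4-6 weeks, and recruitment is described as consecutive. This stands. On a per-participant clock the risk becomes differential referral between units whose wave is known, and the illustration does not carry over.

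**The stronger reading.** A reader might infer that the result is biased towards the intervention by up to 4.8 points, about a quarter of the planned difference. The documents do not support that. The figure compares only the affected wave 2 window with later wave 2 recruits, under assumed hold-back and success rates. Nor does it allow for control recruits who later cross over, or for the primary outcome being read at month 6, when both waves are treated.

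**Conclusion.** The point holds as a defect in the stated safeguard. Two waves with two fixed dates cannot keep wave 2 uncertain once wave 1 is known. Wave 2's foreknowledge is up to about 9-11 weeks rather than 2, which is 82-100% of its control time from wave 1's notice and at least 51% from wave 1's active phase. The flat concealment statement and the claim that recruitment is independent of study phase therefore do not hold as written.

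This rests on units knowing the two-wave schedule or seeing the devices, and the shares use a calendar clock. Three pairs is inferred, but the elimination does not need pairing. The documents do not show that referral was distorted, and the direction and size of any bias are unknown. The crude gap of about 1-2 points is an illustration on one clock, not an estimate.

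This is not a detail left to an analysis plan: the article gives positive assurances that its own design defeats.

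**What to change.** Enrolment is complete, so wording and analysis are what can change.

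1. **Restate the claims** in Study Design and in Informed Consent and Capacity Assessment: allocation was concealed from units only until wave 1's disclosure or transition, and from then on wave 2's allocation and crossover date were inferable.
2. **Adjust for motivation.** Add the baseline weight-motivation VAS as a covariate in the primary GEE and in the mixed models. Its collection at month 0 is inferred from the visit schedule in Outcomes and Measures and should be confirmed.
3. **Check selection descriptively.** Where referral and enrolment dates are held, compare referral counts, baseline BMI and, for enrolled participants, baseline VAS by wave, before and after wave 1's disclosure. Use that one date for all six units; a unit's own disclosure date would miss the exposed period. The listed contents of the screening log (age, sex, diagnosis, BMI) include neither dates nor VAS, so availability must be checked.

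Wave 2 participants enrolled between wave 1's disclosure and their own crossover should stay in the analysis. On the calendar reading they are nearly all of the newly enrolled concurrent controls.

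The cost is a less favourable statement about concealment and a little extra analysis, with no new patients or procedures. Adjusting for the VAS cannot remove selection on traits that were not measured.

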### Intervention Program

The SWIM intervention is a multicomponent digital health program grounded in SCT, designed to enhance self-regulation for weight management. Participants are provided with a Huawei Pro 3 Bluetooth-enabled smart scale and the Huawei Health App (v10.0.2) installed on their personal smartphones. The intervention is coordinated by a multidisciplinary research team, including a trained research assistant for technical setup, a certified nutritionist for dietary content, and a psychiatrist for clinical oversight.

The program follows a hybrid delivery model, initiating in the psychiatric inpatient units of Beijing Anding Hospital and continuing remotely in the participants’ community settings post discharge. During the 2-week transition period, participants receive in-person training on biometric tracking and dietary logging. The intervention lasts for the duration of the assigned wave (5 months for wave 1 and 3 months for wave 2). Participants are instructed to perform weekly weigh-ins and daily dietary logging. To support behavioral change, biweekly educational modules are delivered via WeChat (Tencent) groups. See Multimedia Appendix 1 for the smart scale setup guide and weighing protocol. Furthermore, weekly automated push notifications and personalized feedback messages are sent via messages, with content tailored to each participant’s specific weight trajectory (Table 1).

**Table 1. T1:** Summary of SWIM intervention components.

Components	Delivery method	Frequency
Smart scale weigh-ins	Digital Health App and compatible smart scale	Weekly (at least once per week)
Dietary logging	Digital Health App	Daily (all meals and snacks)
Education session	WeChat groups	Biweekly
Behavior enhancing	Message prompts and tips	Weekly (Automated push notifications and personalized feedback)

### Outcomes and Measures

#### Overview

This study uses a Type 1 hybrid implementation-effectiveness framework to concurrently evaluate clinical outcomes and implementation feasibility. Assessments are conducted at Baseline (month 0) and follow-up intervals at months 1, 2, 3, and 6 (Multimedia Appendix 2). Data collection integrates EHR, laboratory tests, and structured assessments. Baseline assessments take approximately 60 minutes, with 25-minute follow-ups. To ensure long-term sustainability, we use a tiered engagement protocol for nonadherence: automated reminders, followed by counselor outreach (after 2 wk), and finally in-person support for persistent cases. Technical support is provided via video tutorials and a dedicated hotline.

Financial incentives are avoided to favor clinically translatable behavior reinforcement strategies. To address the risk of multiplicity and ensure statistical rigor, we have established a clear hierarchy of endpoints.

To address the risk of multiplicity and ensure statistical rigor, we have established a clear hierarchy of endpoints.

#### Primary Outcome

The primary effectiveness outcome is the proportion of participants achieving ≥5% weight reduction from baseline, assessed at the end of the 6-month study period (month 6). This allows for a final assessment across both waves, regardless of their crossover wave.

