### Primary Objective

The primary objective is to evaluate the effectiveness of the digital intervention on body weight reduction. The primary outcome is the proportion of participants achieving ≥5% weight loss at the end of the intervention phase compared to the control phase. This threshold, along with the ≥7% threshold, is selected based on established evidence linking these levels of weight loss to significant cardiovascular and metabolic health benefits in the SMI population [28-31]. Based on recent trials of tailored digital interventions in similar populations, which reported ≥5% success rates ranging from 15% to 36.6% [32], we anticipate that the intervention will achieve a success rate of at least 40%, significantly higher than the expected 20% success rate in the control phase.

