#### Clinical Effectiveness Analysis

To account for the nested cluster structure and secular time trends inherent in the stepped-wedge design, we use 2 complementary modeling approaches. For the primary binary outcome (≥5% weight loss), a generalized estimating equations model with a logit link function will be used to compare proportions across study phases. For continuous secondary outcomes (eg, mean percentage weight change and BMI reduction), we will use a Linear Mixed-Effects Model. The model is specified as follows:

Yijk=β0+β1⋅Interventionjk+Σγk⋅Timek+Σδm⋅Covariatesijk+αj+ζij+ϵijk

Where:

Yijk represents the continuous outcome for individual i in cluster j at time k.β1estimates the treatment effect (Intervention vs Control); γk represents categorical secular time trends to isolate the intervention’s impact from time-related fluctuations; and δm denotes fixed-effect adjustments for the prespecified covariates. αj is the random intercept for the cluster (clinical unit) to account for ICC; ζij is the random intercept for the individual to account for repeated measurements over time; and ϵijk represents the residual error.

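### The primary outcome is read at month 6, when no unit is on usual care, while the objective and analysis describe a phase comparison; the two must become one contrast with explicit time terms

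*Protocol article*

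**What the plan says.** All references are to the protocol article.

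- **Primary Outcome.** At least 5% weight reduction from baseline, assessed at month 6 in everyone. The reason given is: "This allows for a final assessment across both waves, regardless of their crossover wave".
- **Study Design.** Six units are randomised, three to each of two waves. The two-week transition is described as "occurring at month 1 for wave 1 and month 3 for wave 2". The intervention phase is "active digital monitoring lasting 5 months for wave 1", covering months 2 to 6; for wave 2 it is 3 months, covering months 4 to 6.
- **Primary Objective.** The same outcome is to be compared "at the end of the intervention phase compared to the control phase".
- **Sample Size Estimation.** Success rates of 20% in the control phase and 40% in the intervention phase are assumed. No time point is attached to either.
- **Clinical Effectiveness Analysis.** Two models are introduced together as accounting for clustering and secular trends. For the binary primary outcome, a logit-link GEE "will be used to compare proportions across study phases". The model equation, with its categorical time term, is given for the continuous outcomes only.
- **Statistical Plans, Overview, and Covariate Adjustment.** Time since crossover enters as a time-varying covariate. The Overview places it in the mixed-effects models; the covariate section repeats it for the models in general.
- **Outcomes and Measures, Overview.** Visits are at months 0, 1, 2, 3 and 6.

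**The concern.** One primary outcome carries two different comparisons. The first is a single reading at month 6, when every unit has crossed over, so it contains no usual-care group. The second sets the intervention phase against the control phase, and the phases sit at different distances from baseline: usual care ends at about month 1 or month 3, the intervention at month 6. The outcome is a loss measured from baseline, so it is zero by definition at month 0 and can build up with follow-up whatever the treatment.

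At stake is whether the reported primary result measures the intervention against usual care at all and, if it does, after how much exposure. A reader of the final report would take a month-6 result as the effect of the programme at six months. The randomisation does not supply that comparison directly.

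**Working it through.** **1. Exposure at each visit** (Study Design; months counted from crossover, ignoring the two-week transition)

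| Visit month | 0 | 1 | 2 | 3 | 6 |
|---|---|---|---|---|---|
| Wave 1 | 0 | 0 | 1 | 2 | 5 |
| Wave 2 | 0 | 0 | 0 | 0 | 3 |

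At month 6 the treatment indicator is 1 in all six units. A model with an intercept and treatment has rank 1 of 2 there, so the effect against usual care is not estimable. The wave difference at month 6 is effect(5 months) − effect(3 months).

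This holds whether months are counted by calendar or per participant. The Results section gives data collection from May 2023 to June 2025 and follow-up to January 2026. That points to a per-participant clock, so month is taken below as time since baseline.

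**2. What categorical month identifies.** Regressing the treatment indicator on month indicators over visits 0, 1, 2, 3 and 6, with equal weights, leaves residuals of +0.5 (wave 1) and −0.5 (wave 2) at months 2 and 3, and 0 at months 0, 1 and 6. Only months 2 and 3 have treated and untreated units side by side. If the transition ends at month 1.5, wave 1 has had at most about 1.5 months of active monitoring by month 3, or 2 months counted from the start of transition.

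**3. Follow-up time by phase.** Post-baseline usual-care visits: (1 + 1 + 2 + 3)/4 = 1.75 months. Intervention visits: (2 + 3 + 6 + 6)/4 = 4.25 months.

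**4. The planned effect.** (0.40/0.60)/(0.20/0.80) = 2.67; the article prints about 2.6.

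**5. A phase comparison with no time term and no true effect.** The article gives no usual-care curve, so every path below is an assumption. With p1, p3 and p6 the proportions with at least 5% loss at months 1, 3 and 6:

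Control-phase end p̄ = (p1 + p3)/2; OR = [p6/(1 − p6)] / [p̄/(1 − p̄)].

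| Assumed path | p1 | p3 | p6 | p̄ | OR |
|---|---|---|---|---|---|
| Level from month 3 | 12% | 20% | 20% | 16% | 1.31 |
| Early rise | 10% | 18% | 20% | 14% | 1.54 |
| Square root of time, p6 10% | 4.1% | 7.1% | 10% | 5.6% | 1.88 |
| Square root of time | 8.2% | 14.1% | 20% | 11.2% | 1.99 |
| Steady steps | 5% | 15% | 20% | 10% | 2.25 |
| Linear | 3.3% | 10% | 20% | 6.7% | 3.50 |
| Slow start | 3% | 10% | 20% | 6.5% | 3.60 |
| Linear, p6 30% | 5% | 15% | 30% | 10% | 3.86 |

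**6. Precision of a concurrent contrast.** The stated 82% power is for weight in kg. As a reference for the binary outcome, take one visit, 3 against 3 units, 34 per unit, ICC 0.10, and the full 20% versus 40% already present.

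- Design effect: 1 + 33 × 0.10 = 4.3.
- Effective size per arm: 102/4.3 = 23.7.
- SE = √[(0.16 + 0.24)/23.7] = 0.130, so 0.20/0.130 = 1.54.
- Power: about 34% by this normal approximation (32% with a pooled null variance) and about 22% with a t reference on 4 degrees of freedom.

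Using both visits would add information, by an amount that depends on correlations the article does not give.

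**The case against.** The strongest reply is that the sentence introducing both models, the GEE included, says they account for secular trends. On that reading the GEE carries time, the bias in step 5 disappears, and an effect against usual care is estimable. An article may fairly leave the GEE's terms to a fuller document. This stands. A reader might infer that the planned analysis will manufacture an effect from nothing; the article does not support that. The spurious odds ratios are conditional on time being left out and on assumed curves, and flat curves make them small.

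Second, a reader might infer that the trial can never say anything against usual care. That too goes beyond the article: months 2 and 3 supply a randomised concurrent contrast. With time since crossover in the model, the 5-versus-3-month difference at month 6 informs the slope. A month-6 effect can then be computed, but it depends on the assumed form of the exposure effect, because no untreated unit remains to check it. The Overview also places that covariate in the mixed-effects models, not expressly in the GEE.

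Third, the trial calls itself preliminary, favours estimation over testing and reports 80% intervals for clinical effects. That softens the consequences of imprecision. It does not change what the month-6 reading estimates.

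Fourth, simply moving the endpoint to month 3 would be a poor remedy. Wave-2 device distribution also falls at month 3, weights can no longer be re-timed, and a single-visit comparison of six units is weak. This is accepted, and the fix below avoids it.

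**Conclusion.** The point holds in this form. From the article's own timetable, the month-6 primary outcome has no usual-care comparator and contrasts only about 5 with about 3 months of exposure. The objective, sample size and analysis sections use a different contrast for the same outcome. This is a conflict between stated rules, not omitted detail.

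The size of the consequence depends on the GEE. Without a time term, the phase comparison is biased towards benefit whenever 5% losses accrue under usual care: odds ratios of about 1.3 to 3.9 under no effect on the assumed curves, against a planned 2.67. With categorical month, that confounding is removed under the model. The direct evidence then comes from months 2 and 3 only, and any month-6 effect against usual care is extrapolation. Steps 1 and 2 need only the stated schedule, with equal weighting of visits in step 2. Under a correlated working structure, other visits can contribute, but month 6 does so only by assuming how the effect behaves with exposure.

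**What to change.** 1. Reconcile Primary Objective, Primary Outcome, Sample Size Estimation and Clinical Effectiveness Analysis into one estimand.
2. Define the primary effectiveness contrast as intervention versus usual care for the repeated outcome of at least 5% loss from baseline over the scheduled post-baseline visits, in the GEE with categorical month. Month 0 is zero by definition and cannot contribute.
3. State that this contrast is identified by the concurrent wave comparison at months 2 and 3. Use wave-2 month-3 weights only where they were recorded before device distribution.
4. Report month-6 proportions by wave descriptively, with no claim against control. Label any modelled month-6 effect as extrapolation and state the assumed form of the exposure effect.
5. Drop any phase comparison without time terms.

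No new data are needed, but how many wave-2 month-3 weights qualify under item 3 must be checked. The costs are real. The claim covers only early exposure, up to about 2 months. Precision is lower than the stated power implies; step 6 gives about 22% to 34% for a single visit, even if the full planned effect is present that early. Because follow-up is finished and analysis is under way, the change must be dated and disclosed as made after data collection.
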